### Ethics

The study protocol and associated documents have received approval/favorable opinion from the National Research Ethics Service Committee London - South West (REC number: 08/H0801/113) and from the R&D from participating Primary Care Trusts (PCTs) or Health Boards (HB). Protocol amendments have received REC approval and approval/favorable opinion from participating PCTs and HBs. A senior partner at each participating general practice will be asked to give written informed consent to take part in the study
[27].

## Discussion

This study, together with a previously reported trial in antibiotic prescribing
[28], will provide evidence concerning the feasibility of implementing CRTs using electronic databases and its effectiveness in preventing stroke recurrence and associated vascular events. The methodology developed through this project will have wide potential for application in future research with primary care electronic databases. A key output from the research will therefore be a set of methodological guidelines that will identify and analyze the component tasks of implementing a cluster trial through electronic patient records.

Cluster trials are susceptible to bias and the implementation of a cluster trial within an electronic database offers the opportunity to evaluate such biases. For example, in practices allocated to the intervention the intervention may be associated with increased recruitment rate
[29]. Also, the behavior of professionals at control practices may be modified through their participation in the study even though they are not exposed to the intervention
[28].

These potential biases may be evaluated by comparing number of stroke patients at intervention practices prior to and after the intervention and also comparing changes in secondary prevention activity between non-participating and participating practices.

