### Intervention implementation

Electronic prompts will be installed remotely at intervention general practices. Electronic prompts will be activated during eligible consultations. Consultations will be eligible if the patient is aged ≥18 years and is included on the practice stroke register. During consultations with patients who have previously had a stroke, primary care professionals will see the prompts which remind them of evidence-based guidelines for secondary prevention of stroke. The main focus is on targets for control of blood pressure and cholesterol levels, appropriate prescribing of aspirin and antiplatelet drugs, and enhanced recording of stroke type (ischemic or hemorrhagic). The prompts will also provide GPs with supporting information, links to evidence that supports the recommendations, and options to print patient information. The decision on whether to follow the treatment suggestions included in the prompts will be at the discretion of the GP. The GP will also be able to terminate display of the prompt at any time. At the start of the study, a letter containing instructions on the use of the prompts will be sent to general practices in the intervention trial arm for circulation to participating general practitioners. All control practices will be sent a letter reminding them to record any relevant consultation for eligible stroke patients and to notify any adverse events. Three months into the study, all intervention practices will receive an email reminder containing instructions about the prompts including aims and implementation.

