### Outcome evaluation

The evaluation of outcomes will be through analysis of routinely-collected GPRD data during a defined study period, while historical information will be used to assess the baseline characteristics of the study patients. Information routinely collected into GPRD for all registered patients includes medical history, use of medicines, hospitalizations and other resource use, smoking history, laboratory tests, letters from specialists or hospitals. GPRD also now links patients in GPRD to the English Hospital Episode Statistics, with detailed information on date, duration, and reason for hospitalization. Availability of data for all registered patients has potential to minimize biases from subject selection/recruitment.

Electronic records will be included in analyses for all patients on the practice’s stroke register. Participants that were diagnosed with transient ischemic attacks only will be excluded. The primary outcome measure is the mean systolic BP after 12 months. Modeling will be used to utilize BP values measured over time during the intervention period.
[21] Secondary outcomes will be mean diastolic blood pressure; mean cholesterol concentration; proportion of patients whose eligibility for anticoagulants/antiplatelet drugs is defined; proportion of eligible patients that receive anticoagulant/antiplatelet drugs; prescription adherence with prescribed medicines; occurrence and hospitalization with vascular events including TIA/stroke, myocardial infarction, new-onset angina, and mortality. In light of recent changes in guidelines for anti-platelet treatment, an additional outcome will be the proportion of patients that received clopidogrel as the first drug of choice. Recurrent stroke events will be validated through anonymized records obtained from practices. Linked HES data may be used to evaluate hospital utilization. The method of Generalized Estimating Equations will be implemented to allow for clustering by practice, providing an analytical framework for both binary and continuous outcomes
[22]. Last value carried forward and multiple imputation will be used to deal with missing values.

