### Sample size calculation

The sample size calculation is based on a comparison between the trial intervention and usual care, represented by the targets included in the quality and outcomes framework (QOF) for stroke. Thus the QOF recommends a blood pressure target for stroke patients of 150/90 mm Hg while the trial prompts, following the ICSWP guidelines, recommend a target of 130/80 mm Hg. The age-standardized incidence of first stroke is between 1.74 and 2.16 per 1,000 in England
[2,23]. In 375 GPRD practices in 2006, there were approximately 14.5 first strokes per practice per year (ISAC protocol 07–027). We propose to include for analysis all subjects whose first stroke was in the 2 years preceding the intervention start date, giving about 29 subjects per practice eligible for analysis. If the standard deviation of systolic BP in these subjects is 19 mm Hg
[24,25] with an ICC by general practice of 0.032
[26], with a two-sided alpha=0.05, power=0.8, then to detect a 2.75 mm Hg difference in systolic blood pressure, about 99 practices will be required with 50 receiving the active intervention. This represents an effect size of 0.14. In reality, the number of patients per practice will be variable and the coefficient of variation of practice size may be approximately 0.65
[27]. This means that the effective number of practices is approximately 83 and the detectable difference in systolic BP will be approximately 3mm Hg. Analysis of GPRD data for stroke shows a high proportion of stroke patients had blood pressure recordings in 2006 with a mean of three blood pressure records per patient.

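### Two conflicting analysis populations leave room for late-coded strokes to enter differently by arm, and the one stated check on patient numbers has no concurrent control

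*Protocol article*

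**What the plan says.** The article states who will be analysed in two places.

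- Outcome evaluation: "Electronic records will be included in analyses for all patients on the practice’s stroke register". One exclusion follows: "Participants that were diagnosed with transient ischemic attacks only will be excluded". No date of entry is given.
- Sample size calculation: the proposal is to "include for analysis all subjects whose first stroke was in the 2 years preceding the intervention start date".

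Intervention implementation says which patients trigger a prompt: "Consultations will be eligible if the patient is aged ≥18 years and is included on the practice stroke register". One stated focus of the prompts is the recording of stroke type. Control practices get a recording reminder of their own: "All control practices will be sent a letter reminding them to record any relevant consultation for eligible stroke patients".

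The Discussion names the bias at issue, saying that "in practices allocated to the intervention the intervention may be associated with increased recruitment rate". It then suggests two evaluations. The first is "comparing number of stroke patients at intervention practices prior to and after the intervention". The second compares changes in secondary prevention activity between practices in the trial and practices outside it.

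**The concern.** In a cluster trial the practices are randomized, and the patients are comparable between arms only if membership of the analysed group does not depend on allocation. Practices here know their arm, and recording is influenced in both arms by different means: prompts, an instruction letter and a three-month reminder in one, a recording letter in the other. If patients can join the analysed set after allocation, and the added patients differ in blood pressure from those already there, part of the difference in mean systolic pressure reflects who was recorded rather than how they were treated.

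The article acknowledges this risk, so its population rule should close the route as far as possible and its check should be able to reveal what remains. As written, the two population statements disagree, neither is tied to the date of recording, and the check on numbers uses one arm only. The article also presents methodological guidance for cluster trials in electronic records as a key output, which is a further reason for the check to be sound.

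**Working it through.** **1. The plan's own figures.** Inputs from Sample size calculation: SD 19 mm Hg, ICC 0.032, 29 patients per practice, difference 2.75 mm Hg, two-sided alpha 0.05, power 0.8, coefficient of variation of practice size 0.65.

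- Patients per arm without clustering: 2 × (19 × (1.960 + 0.842) / 2.75)² = 749.3, so 750.
- Design effect: 1 + (29 − 1) × 0.032 = 1.896.
- Practices per arm: 750 × 1.896 / 29 = 49.03, so 98 to 99 in total (stated: about 99).
- Design effect with unequal sizes: 1 + ((1 + 0.65²) × 29 − 1) × 0.032 = 2.288.
- Effective practices: 99 × 1.896 / 2.288 = 82.0 (stated: about 83). Detectable difference 3.01 mm Hg with 82 and 2.99 with 83 (stated: about 3).

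The figures reproduce. The 29 is 2 years × 14.5 first strokes per practice per year, so the sample size rests on the narrower, pre-intervention population.

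**2. The two population rules side by side.**

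| Patient | Outcome evaluation | Sample size calculation |
|---|---|---|
| First stroke within the 2 years, recorded before allocation | in | in |
| First stroke more than 2 years before intervention start | in | out |
| First stroke during the trial year | in | out |
| First stroke within the 2 years, coded only after allocation | in | in |
| TIA-only record reclassified as stroke after allocation | in | in, if the stroke date falls in the window |

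Rows 2 and 3 are the conflict. Row 3 alone is about 14.5 patients per practice on a base of 29, expected in either arm. Rows 4 and 5 remain open under both rules, because the narrower rule is set by stroke date.

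**3. What the count check can show.** Let s be the secular change in registered stroke patients, b the change caused by the intervention, and c the change caused by the control letter. The before-after count in intervention practices estimates s + b: one observed quantity, two unknowns. It can rise with b = 0, or stay flat when s and b have opposite signs. The between-arm difference in change is (s + b) − (s + c) = b − c, which removes s and is the differential entry that could bias the comparison. The second suggested evaluation measures activity, not patient numbers, and does not compare the randomized arms, so it gives neither quantity.

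**4. Possible size (illustration; inputs assumed, not from the documents).** Suppose extra registrations, as a fraction e of the existing patients, occur in the intervention arm only, and the added patients differ by D in mean systolic pressure. Bias = D × e / (1 + e), in mm Hg:

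| e | D = 3 | D = 5 | D = 10 |
|---|---|---|---|
| 2% | 0.06 | 0.10 | 0.20 |
| 5% | 0.14 | 0.24 | 0.48 |
| 10% | 0.27 | 0.45 | 0.91 |
| 20% | 0.50 | 0.83 | 1.67 |

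The range is 2% to 61% of 2.75 mm Hg.

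**The case against.** A reader might infer that nothing stops patients entering after allocation, that the before-after count is the only safeguard, and that the bias is neither prevented nor detectable. The documents do not support that.

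- The window in Sample size calculation closes before the intervention begins. If it governs, first strokes during the trial year are out, and only late coding and reclassification remain.
- The same sentence of the Discussion gives a second evaluation with a concurrent comparator, although it addresses altered behaviour through taking part rather than patient numbers.
- Prompts appear only for patients already registered, so they do not directly prompt the finding of unregistered ones. This narrows the route. It does not exclude wider changes in coding, or reclassification where attention is drawn to stroke type.
- Routine records cover all registered patients in both arms, and Outcome evaluation notes their potential to limit selection bias. Entries by arm could be counted at any time.

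It is also fair that the Discussion speaks of what may be evaluated, by way of example, and that a full protocol or analysis plan may say more. That lowers the weight of the point on the check. It does not remove the conflict between two stated population rules, which concerns what this article itself fixes.

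The upper end of the illustration is hard to reach under the narrower rule: e = 20% means 29 × 0.20 = 5.8 extra patients per practice, or 5.8 / 14.5 = 40% of a year's first strokes, all coded late and only in one arm. Additions in control practices, which also get a recording letter, could offset part of it.

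**Conclusion.** The point holds in limited form. The two sections define different analysis populations and must be reconciled. Even the narrower one admits strokes coded late or reclassified from TIA after allocation, because it is anchored to stroke date and not to record date. The one stated check on patient numbers cannot separate differential entry from secular change in coding.

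The documents do not show that such bias will occur, nor how large it would be. The range of 0.06 to 1.67 mm Hg rests wholly on assumed inputs: the low end would not matter, and the high end would be a large part of the 2.75 to 3 mm Hg the trial is built to detect. A claim that the bias could take up half the target should be read only as an assumed worst case. The change is worth making because it costs little, not because harm has been demonstrated.

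**What to change.** 1. Reconcile Outcome evaluation with Sample size calculation, so that one analysis population is stated in both.
2. Define the primary cohort in both arms from records entered on or before the practice's allocation date, a date that every practice has. Apply the TIA-only exclusion as coded at that date. Analyse patients recorded later in a sensitivity analysis only.
3. Replace the before-after count with a between-arm comparison of the change in register counts and in new stroke codes, allowing for clustering by practice. The comparison of activity with non-participating practices can stay for its own purpose.

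Cost: wording in the protocol or analysis plan, plus the need for either a date of record entry or a copy of the register at allocation. A few late-coded patients leave the primary analysis. The sample size is unaffected, since its 29 per practice already comes from a pre-intervention window.

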## Trial status

Practice recruitment stage.

## Abbreviations

CRT: Cluster randomized trials; GPRD: General Practice Research Database; HB: Health boards; HES: Hospital episode statistics; ICSWP: Intercollegiate Stroke Working Party; ITT: Intention to treat; KCL: King’s College London; MHRA: Medicines and Healthcare products Regulatory Agency; NHS: National Health Service; QOF: Quality and Outcomes Framework; PCT: Primary care trusts; REC: Research and Ethics Committee.
